## Abstract

**Objectives:**

Inhibitory control deficits are considered a key pathogenic factor in anxiety disorders. To assess inhibitory control, the antisaccade task is a well-established measure that assesses antisaccade performance via latencies and error rates. The present study follows three aims: (1) to investigate inhibitory control via antisaccade latencies and errors in an antisaccade task, and their associations with multiple measures of fear in patients with spider phobia (SP) versus healthy controls (HC), (2) to investigate the modifiability of antisaccade performance via a fear-specific antisaccade training in patients with SP and HC, and (3) to explore associations between putative training-induced changes in antisaccade performance in SPs and changes in diverse measures of fear.

**Methods:**

Towards aim 1, we assess antisaccade latencies (primary outcome) and error rates (secondary outcome) in an emotional antisaccade task. Further, the baseline assessment includes assessments of psychophysiological, behavioral, and psychometric indices of fear in patients with SP and HCs. To address aim 2, we compare effects of a fear-specific antisaccade training with effects of a prosaccade training as a control condition. The primary and secondary outcomes are reassessed at a post-1-assessment in both SPs and HCs. Aim 3 employs a cross-over design and is piloted in patients with SP, only. Towards this aim, primary and secondary outcomes, as well as psychophysiological, behavioral, and psychometric measures of fear are reassessed at a post-2-assessment after the second training block.

**Conclusion:**

This study aims to better understand inhibitory control processes and their modifiability in spider phobia. If successful, antisaccade training may assist in the treatment of specific phobia by directly targeting the putative underlying inhibitory control deficits. This study has been preregistered with ISRCTN (ID: ISRCTN12918583) on 28th February 2022.

## Background

Specific phobia constitutes the most prevalent anxiety disorder with a prevalence ranging from 1.5% to 14.4% in adults [1]. Specific phobia is characterized by excessive fear of a specific object (e.g. spiders) or a specific situation [2]. Real or expected confrontation with the fear-evoking stimulus elicits a direct fear reaction, thus prompting habitual avoidance of this stimulus. While specific phobia can be treated effectively [2], studies show that about one-third of patients do not benefit from common first-line treatments [3, 4]. A better understanding of the neurocognitive underpinnings of specific phobia as a model for anxiety disorders may pave the way for developing mechanism-informed targeted interventions that could add to the existing methods of treatment and address the problem of non-response to treatment.

Anxiety can be characterized by a fast initial shift in attention, in favor of threatening stimuli [5]. The Attentional-Control Theory distinguishes two systems that are involved in attentional control: a goal-driven top-down system and a stimulus-driven bottom-up system [6]. The presence of a fear-evoking stimulus is assumed to disrupt the balance of these systems in favor of bottom-up processing, causing a shift of attention towards the fear-evoking stimulus. From an evolutionary perspective, this is a highly adaptive mechanism preparing organisms for fast reactions towards (potential) threats [7]. Yet, if too sensitive, this mechanism may contribute to pathological anxiety, which is–amongst other aspects (e.g., avoidance, increased psychophysiological responses [8])–characterized by an inability to adequately inhibit bottom-up-driven attentional processes.

A well-established experimental task to assess inhibitory control is the antisaccade task [9]. In the antisaccade task, participants are instructed to look in the opposite direction of a peripherally presented visual stimulus. Indices of reduced inhibitory control are prolonged latencies of correct antisaccades and increased error rates (gaze at the visual stimulus, instead of the opposite direction). While the latency of correct antisaccades constitutes a measure of inhibitory control efficiency, the error rate reflects the effectiveness of inhibitory control performance [10]. Antisaccades have been used in a variety of different psychiatric populations to assess inhibitory control. Perhaps most prominently, the antisaccade task has been applied in the research of psychotic and schizophrenic disorders [9], however it has also been used to study inhibitory control in obsessive-compulsive disorder [11], post-traumatic stress disorder [12], binge-eating disorder [13], attentional-deficit-hyperactivity disorder [14], and alcohol use disorder [15]. Additionally, research has identified reduced inhibitory control efficiency, indexed by prolonged latencies of correct antisaccades, in a multitude of highly anxious, yet subclinical participants [16, 17]. Reduced inhibitory control at high levels of (dispositional) anxiety is further reported in a meta-analysis investigating the association between inhibitory control and anxiety in a multitude of different tasks [18]. In line with this, it is considered a risk and maintaining factor of pathological anxiety [19]. Surprisingly, there are no studies investigating inhibitory control via antisaccade performance in patients with specific phobia. Thus, the profile of probable inhibitory control deficits in patients with specific phobia and its association with other indices of fear, like avoidance behavior and psychophysiological responses, remains elusive. Furthermore, it is unclear, whether patients with specific phobia show impaired inhibitory control only in response to phobia-relevant stimuli or if they exhibit a general deficit in inhibitory control.

In previous studies, antisaccade training improved antisaccade performance in non-clinical and clinical samples [20, 21]. In a sample of patients with binge eating disorder, antisaccade training improved not only antisaccade performance in response to disorder specific stimuli (i.e., high-caloric food), but was also associated with a significant decrease of binge eating incidents. However, no changes could be found in psychometric measures associated with binge eating (e.g., food craving [21]). To date, there are no studies investigating the trainability of antisaccade performance in specific phobia.

To further elucidate the role of inhibitory control performance in specific phobia, the present study investigates antisaccade performance in patients with spider phobia (SP) compared to healthy controls (HC). As the literature on (dispositional) anxiety and inhibitory control mainly indicates inhibitory control deficits with regard to efficiency rather than effectiveness, antisaccade latency serves as the primary outcome. Antisaccade error rate (as a marker of inhibitory control effectiveness) is investigated as a secondary outcome. Our study follows three main aims: First, patients with spider phobia (as a model anxiety disorder) are investigated via the antisaccade task regarding potential inhibitory control deficits and their associations to certain stimulus materials (phobia-related versus neutral), psychophysiological (heart rate, skin conductance, startle-response), behavioral and psychometric measures of fear (aim 1). This aim employs a proof-of-concept mixed factorial design with the between subject factors group (SPs vs. HCs) and the within-subject factor stimulus material (phobia-related vs. neutral). Second, the modifiability of inhibitory control through a fear-specific antisaccade training is piloted (aim 2). This aim employs an exploratory randomized controlled parallel group design with two training conditions (antisaccade training vs. control) that is realized in SPs and HCs. Changes in antisaccade performance from baseline to post-1-assessment, and their dependence on stimulus material is assessed. Third, putative changes in inhibitory control performance following the training are investigated regarding associations to changes in psychophysiological, behavioral, and psychometric measures of fear in SPs, therefore exploring possible therapeutic utility (aim 3). This aim employs an exploratory cross-over design in SPs only, i.e. patients switch training conditions after the post-1-assessment, and are assessed regarding antisaccade performance, psychophysiological (heart rate, skin conductance, startle-response), behavioral and psychometric measures of fear at post-2-assessment.

## Methods

### Participants

Participants with a specific phobia of the animal subtype (spiders) and HCs are recruited at the University of Siegen and from the general population. Interested participants are invited to a short telephone screening (~ 10 minutes) and then enrolled in a more extensive clinical interview (~ 1 hour) via telephone to assess further eligibility, conducted by trained research assistants. SPs have to fulfill the criteria of specific phobia according to the Diagnostic and Statistical Manual of Mental Disorders-IV (SCID-I, Section F [22], while HCs must not fulfill the criteria of spider phobia and not exceed a value of 19 points in the Spider Phobia Questionnaire (SPQ) [23]. Inclusion criteria for both groups are an age between 18 and 65 years, normal or corrected to normal vision, as well as normal hearing. Exclusion criteria are any psychiatric condition (except spider phobia, as well as mild to moderate depressive episodes in the past in patients with SP) assessed via the Mini-International Neuropsychiatric Interview (MINI) [24]. Furthermore, any history of neurological disorders, current intake of Benzodiazepines or Barbiturates, astigmatism, hearing disorders, subjective auditory hypersensitivity, regular nicotine consumption (> 5 cigarettes/day) or known allergy to bites of insects and arachnids lead to exclusion.

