### Sample size

Based on two studies using the antisaccade task in clinical samples, we calculated two a-priori power analyses using G*Power 3.1 [25] for ANOVAs (Analyses of Variance) to detect large effect sizes (Cohen´s *f* = .40, *α* = .05, power = .85) in our primary outcome (i.e. antisaccade latencies) at baseline (aim 1) [12] and for the training effect (aim 2) [21]. Results indicated a required total sample size of 59 participants (30 per group).

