#### Statistical analyses

In the following, planned analyses will be described in brief. Further details on statistical analyses for aim 1 and aim 2, can be found in the detailed statistical analyses protocols for each aim. For further details on aim 3, a statistical analyses protocols will be preregistered with Current Controlled Trials (ID: ISRCTN12918583).

Corresponding to aim 1 of the study, baseline differences in antisaccade performance between participants with SP and HCs will be investigated using general linear modeling with antisaccade latency and antisaccade error as outcome respectively. Diagnosis will be entered as a between-subject-factor, stimulus category as a within-subject factor, resulting in a 2x2 design. To investigate associations between multimodal measures of fear (psychophysiological responses, BAT and SPQ scores) and antisaccade performance in SPs, multiple regression analyses will be conducted with the primary and secondary outcome as dependent variables, respectively. If relevant demographic or psychometric measures differ between groups, these measures will be entered as covariates (for statistical analysis plan see ISRCTN12918583). Corresponding to aim 2 of the study, general linear modelling will be conducted with diagnosis and intervention (antisaccade training vs. prosaccade training) as between-subject factors, as well as time and stimulus category as within-subject factors, resulting in a 2x2x2 design, including antisaccade latency and error rate as outcomes. Again, potential confounds showing group differences will be entered as covariates (for statistical analysis plan see ISRCTN12918583).

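### Aim 1 adjusts the patient-versus-control comparison for age and sex only if the groups are seen to differ, which leaves a small, avoidable bias (minor)

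*Protocol article*

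**What the plan says.** The Participants section gives both groups the same age window and sensory criteria: "Inclusion criteria for both groups are an age between 18 and 65 years, normal or corrected to normal vision, as well as normal hearing". Both groups also share their sources: "Participants with a specific phobia of the animal subtype (spiders) and HCs are recruited at the University of Siegen and from the general population". The extra HC criteria concern the absence of spider phobia and a ceiling on the Spider Phobia Questionnaire. None links the age or sex mix of the HCs to that of the SPs.

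For the aim 1 model, the Statistical analyses section says "Diagnosis will be entered as a between-subject-factor, stimulus category as a within-subject factor, resulting in a 2x2 design". Its provision for group differences is "If relevant demographic or psychometric measures differ between groups, these measures will be entered as covariates", with a pointer to a registered analysis plan that is not shown. The Sample size section powers the study "to detect large effect sizes (Cohen´s *f* = .40, *α* = .05, power = .85) in our primary outcome" and reports the result as "Results indicated a required total sample size of 59 participants (30 per group)".

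**The concern.** The block randomisation in the protocol assigns training, not diagnosis. The aim 1 latency contrast is therefore observational, and its reading as a phobia-related deficit depends on how comparable the groups are. The age window spans 47 years (65 − 18). The same two sources can still contribute in different proportions to SPs and HCs.

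If latency varies with age, an age gap between the groups adds to the diagnosis effect. The plan's protection is an adjustment that depends on an observed difference. With 30 per group, a comparison of mean ages has little power against a moderate gap, so the adjustment will often not be made when it would help. At stake is some bias in the estimated group difference in latency and, to a lesser degree, in its test.

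**Working it through.** **Inputs from the article.** f = .40, alpha = .05, power = .85, total 59, 30 per group; adjustment only if the groups differ.

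**Assumed inputs (not in the article).** Groups differ when p < .05 on a two-sample t-test of age; true mean age gap 5 years; age SD 12.5 years, so the gap is 5 / 12.5 = 0.40 SD; latency SD 40 ms; latency slope 0.5, 1.0 or 1.5 ms per year; no true diagnosis effect.

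**Step 1: the stated sample size.** With a noncentral F, λ = N·f², and 1 and N − 2 degrees of freedom, power is .8494 at N = 58 and .8555 at N = 59. The stated 59 reproduces. For two groups f = .40 is d = .80, which is 0.80 × 40 = 32 ms at the assumed SD.

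**Step 2: how often the trigger fires.** At 30 per group the observed age gap must exceed t(.975; 58) × SD × √(2/30) = 2.00 × 12.5 × 0.258 ≈ 6.5 years to reach p < .05. The noncentrality for a true gap of 0.40 SD is 0.40 × √(30/2) = 1.55, which gives a power of .33. For a true gap of 0.50 SD, power is about .48.

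**Step 3: no adjustment at all.** This is not the plan; it is shown only as a reference. The bias is slope × 5 years = 2.5, 5.0 or 7.5 ms. A t-test at 30 per group with SD 40 then rejects in 5.7%, 7.6% or 11.0% of trials.

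**Step 4: the planned rule.** Age is entered as a covariate only when its own test gives p < .05. Simulation with 40,000 runs per slope gave:

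| Slope (ms/year) | False positives, planned rule | False positives, age always entered | Mean bias, planned rule (ms) | Mean bias where trigger misses (ms) |
|---|---|---|---|---|
| 0.5 | 5.2% | 5.2% | 1.1 | 1.7 |
| 1.0 | 5.4% | 5.1% | 2.3 | 3.3 |
| 1.5 | 5.6% | 5.0% | 3.3 | 4.9 |

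The Monte Carlo standard error of these rates is √(.05 × .95 / 40,000) ≈ 0.1 percentage point, so the excess at 0.5 ms per year cannot be told from zero. A repeat with 100,000 runs per slope gave 5.0%, 5.3% and 5.6% for the planned rule, and a mean bias near zero with age always entered.

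**Step 5: why the residual is smaller than in step 3.** Samples that miss the trigger are those in which the observed age gap came out small. Their mean gap is about 3.3 / 1.0 = 3.3 years, not 5. Triggered samples are adjusted and contribute essentially no bias. Overall bias is therefore about 0.67 times the untriggered bias, for example 0.67 × 4.9 = 3.3 ms.

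**Step 6: a wider range.** With age–latency correlations of 0.2 to 0.5 and true gaps of 0 to 0.8 SD (20,000 runs each), false-positive rates were 4.3 to 6.0% under the planned rule and 4.7 to 5.2% with age always entered. The worst case for the planned rule was a correlation of 0.5 with a gap of 0.5 SD.

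**The case against.** The strongest reply is that the article has already provided for this problem. Both groups share one age criterion and the same two sources, and demographics that differ are to be entered as covariates. The details, including what counts as different and which measures are relevant, belong in the registered analysis plan, so their absence from a condensed article proves nothing. Silence on matching does not show that there is none. Aim 1 is also described as proof of concept.

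Most of this stands. A reader might infer that aim 1 could take an age difference for a phobia deficit, with a false-positive rate of 6 to 11%. The article does not support that: those rates belong to an analysis that never adjusts (step 3), and the stated rule brings them down to about 5.2 to 5.6% under the same assumptions. A reader might also infer that HCs will be younger because students are recruited, so that bias favours the hypothesis. Nothing says HCs draw more heavily on the campus than SPs do, so the direction is conjecture. The comparison across stimulus categories is within-subject and is exposed only if the age effect itself differs between spider and flower stimuli.

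What the reply does not remove is the condition itself. The article makes adjustment depend on an observed difference, and any such trigger lets through the gaps it fails to detect. Nor can an analysis plan change who is enrolled.

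**Conclusion.** The point holds in a limited form and is minor. Under the stated rule, read as a p < .05 trigger, a true 0.4 SD age gap goes unadjusted in about two thirds of samples. The resulting mean bias is about 1 to 3 ms overall and 1.7 to 5 ms where the trigger misses. Against the powered effect of 32 ms, the overall bias is 1.1 / 32 ≈ 3% to 3.3 / 32 ≈ 10%. It would weigh more if the true deficit were smaller than planned for. The effect on type I error is at most about 0.6 percentage points in this example, and about 1 point over the wider range.

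The age gap, both SDs, the slope and the trigger are assumptions. The simulations take a linear age effect with overlapping ages and do not model sex. With poor overlap or a curved age effect, covariate adjustment would protect less than shown.

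**What to change.** In the aim 1 models for latency and error rate, enter age and sex as covariates regardless of any baseline comparison. This replaces the conditional wording for these two variables only. Make the same change in the registered plan if it carries the same condition.

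Where HC recruitment is still open, also frequency-match HCs to SPs on sex and broad age bands (for example 18–29, 30–44 and 45–65) at the existing telephone screening. Matching secures age overlap, which a covariate cannot supply.

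The cost is two model degrees of freedom (error df from 58 to 56 with 60 participants), some recruitment bookkeeping and possibly a few declined HC volunteers. If enrolment is too advanced for matching, the covariate change alone removes the residual age bias when the age effect is linear.

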## Discussion

The present study is designed to compare the antisaccade performance of SPs to a HC group and to examine the putative potential of an antisaccade training with phobia-related stimuli to increase inhibitory control in specific phobia. It also aims to explore associations between antisaccade performance and multimodal psychophysiological, behavioral, and psychometric measures of fear.

Focusing on the comparison of SPs and HCs (aim 1), a decreased antisaccade performance in SPs would yield evidence for reduced inhibitory control functions in SPs. This finding would extend previous findings, which have yielded evidence for associations between antisaccade performance and subclinical anxiety levels [16, 17], to clinically anxious individuals. Thereby, such findings would provide further evidence for a key role of inhibitory control processes in the pathogenesis and maintenance of specific phobia. Such evidence from the study of antisaccade performance would complement previous evidence from the field of fear conditioning, which has suggested deficient inhibitory learning processes and reduced inhibition of fear responses to safe stimuli in patients with pathological anxiety [50] and non-responders to exposure therapy in spider phobia [51]. As spider phobia is used as a model disorder for anxiety disorders more broadly, results could also serve as foundation for research on a wider range of anxiety disorders.

To estimate the clinical relevance of putative deficits in antisaccade performance (i.e., inhibitory control), it seems pivotal to shed light to its link with symptoms of fear. We therefore investigate relationships between antisaccade performance and multimodal measures of fear (e.g., psychophysiological fear responses, avoidance behavior as assessed via the BAT, and self-reported symptoms as assessed via the SPQ). The finding of significant associations could broaden our knowledge on the mechanistic basis of specific aspects of the fear response and form the basis for future research on a potential (causal) role of inhibitory control on fear-associated symptoms.

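### Past depressive episodes are accepted in patients but not in controls, so the aim 1 group main effect is partly confounded with depression history

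*Protocol article*

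**What the plan says.** The Participants section gives one list of psychiatric exclusions, assessed with the MINI, for both groups. Any psychiatric condition excludes, with the exception of spider phobia, "as well as mild to moderate depressive episodes in the past in patients with SP". The allowance for past depression is worded for patients with spider phobia (SPs) only. The lines on healthy controls (HCs) add requirements and no matching allowance: "HCs must not fulfill the criteria of spider phobia and not exceed a value of 19 points".

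Under Statistical analyses, aim 1 is a comparison of these two groups at baseline: "Diagnosis will be entered as a between-subject-factor, stimulus category as a within-subject factor, resulting in a 2x2 design". Latency is the primary outcome and error rate the secondary one. The stated handling of group differences is conditional: "If relevant demographic or psychometric measures differ between groups, these measures will be entered as covariates". Depression history is not named there. The section describes the analyses in brief and refers to separate analysis plans for aims 1 and 2.

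The Background asks whether patients show "impaired inhibitory control only in response to phobia-relevant stimuli or if they exhibit a general deficit in inhibitory control". The Discussion states how a group difference will be read: "a decreased antisaccade performance in SPs would yield evidence for reduced inhibitory control functions in SPs".

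**The concern.** Randomisation in this trial covers the order of training, not diagnosis. At baseline, only the eligibility rules make SPs and HCs comparable, and on depression history those rules work in opposite directions. A control with a past mild or moderate episode is turned away, while a patient with the same history is enrolled. If such a history has any lasting association with antisaccade performance, part of the SP-HC difference would appear even if phobia had no effect.

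The exposed quantity is the group main effect. It is also what decides between the two readings posed in the Background, because a general deficit is a difference that shows across both stimulus types. The Discussion attributes a deficit to spider phobia and does not mention past depression as an alternative.

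**Working it through.** **Plan's own figure.** Inputs from Sample size: f = .40, alpha = .05, power = .85, result 59 in total (30 per group). For a two-group fixed-effects ANOVA with noncentrality f²N, power is 0.849 at N = 58 and 0.856 at N = 59, so 59 reproduces. For two equal groups d = 2f = 0.80. At N = 60, power is 0.861. The concern does not affect this figure.

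**Size of the spurious difference.** Let q be the share of SPs with a past episode and δ the shift in the outcome, in SD units, that goes with that history. The share in HCs is 0 by the eligibility rule. With no phobia effect, the expected group difference is

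q × δ − 0 × δ = q × δ.

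The documents give neither q nor δ. Both ranges are assumptions: q = 10-30%, δ = 0.3-0.8 SD.

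- Low corner: 0.10 × 0.3 = 0.03 SD
- Illustrative middle: 0.20 × 0.5 = 0.10 SD
- Another middle case: 0.30 × 0.5 = 0.15 SD
- High corner: 0.30 × 0.8 = 0.24 SD

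**False-positive rate.** Two-sided t test, 30 per group, 58 degrees of freedom, noncentrality q × δ × √(30/2):

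| Spurious shift (SD) | Noncentrality | Rejection rate | Share of planned 0.80 SD |
|---|---|---|---|
| 0.03 | 0.12 | 5.1% | 3.75% |
| 0.10 | 0.39 | 6.7% | 12.5% |
| 0.15 | 0.58 | 8.8% | 18.75% |
| 0.24 | 0.93 | 15.0% | 30% |

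**Which contrasts are exposed.**

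- *Group main effect:* fully exposed, because the shift q × δ enters the SP mean at both stimulus types.
- *Group × stimulus interaction:* this is the SP-HC difference for spiders minus that for flowers. A shift common to both stimuli gives q × δ − q × δ = 0. Only a history effect that itself differs by stimulus would remain.
- *Aim 1 regressions on fear measures:* run within SPs, so the unequal rule between groups does not enter.
- *Aim 2 training contrast:* randomised, so it is not biased in the same way.

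**Whether adjustment can work.** Write the model as outcome = a + b × SP + c × history. Three cells exist: HC has mean a, SP without history a + b, and SP with history a + b + c. Three parameters fit three means, so the estimate of b is the mean of SPs without history minus the mean of HCs. Diagnosis and history are collinear only if every SP has a history. Without other covariates, entering the indicator and dropping the affected SPs therefore give the same point estimate of the group difference.

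**Precision of the restricted comparison.** Power at d = 0.80 against 30 HCs, two-sided 5%: 86% with 30 SPs, 84% with 27 (10% removed), 79% with 21 (30% removed).

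**The case against.** The case against is substantial, and much of it stands.

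- *The exception is stated openly.* It is a design choice and not a contradiction. It is also narrow: only past, non-severe depression is allowed. This stands, but it does not remove the asymmetry.
- *The documents do not show that past depression affects antisaccades.* The Background says "Antisaccades have been used in a variety of different psychiatric populations to assess inhibitory control", and a reader might infer that it supports depression as a rival explanation. It does not. The conditions named there are psychotic, obsessive-compulsive, post-traumatic stress, binge-eating, attention-deficit and alcohol use disorders. Depression is not among them, and the exception for SPs does not extend to any of them. The effect of past depression is an assumption, and the upper value of 0.8 SD equals the planned effect of phobia itself.
- *Covariate adjustment.* Because no HC has a past episode, a reader might conclude that the covariate rule cannot deal with the problem. The algebra above shows otherwise. What can be said is that the rule does not name depression history.
- *The analysis plan is not shown.* The covariate list and any sensitivity analysis may be there, and their absence from the article is no fault. The point rests on the eligibility rule and the planned interpretation, both stated in the article.
- *Changing eligibility for remaining participants.* A reader might take this as the natural remedy. It would mix two control definitions in one sample, and an equal rule does not guarantee equal shares with a history.

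**Conclusion.** The point holds as a modest one. The eligibility rule allows a depression history in SPs and none in HCs, so the SP-HC main effect on latency and error rate is partly confounded with that history. It does not follow that aim 1 as a whole is compromised: the group × stimulus interaction is largely protected, and the within-SP regressions and the randomised training contrast are not affected in the same way.

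The size cannot be derived from the documents. Under the assumed 10-30% of SPs and 0.3-0.8 SD, the false-positive rate for the main effect runs from practically nominal to three times nominal. Wider assumptions give larger figures (50% of SPs and 0.8 SD give 0.40 SD and 33%), but nothing in the documents supports choosing them. If few SPs have a past episode, the matter is negligible, and the trial's own interview data can show whether that is so.

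**What to change.** Prespecify three things for aim 1:

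1. Report how many SPs had a past mild or moderate depressive episode.
2. Repeat the SP-HC comparison of latency and error rate without those SPs or, equivalently for the group difference, with a history indicator in the model.
3. Report both estimates with confidence intervals, and attribute a general deficit to phobia with caution if the estimate shrinks materially.

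Judge shrinkage from the estimates and intervals, not from whether significance is retained, because the repeat analysis has fewer SPs. A change in the eligibility criteria is not needed.

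The cost is one extra analysis on data that the MINI already supplies, and slightly lower precision in that analysis. The planned sample size does not change.
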